#### Visit 3: Treatment Progress Meeting

The clinician will follow-up with the caregiver for 3 months (+21 or –21 days) after the participant receives an ASD diagnosis to discuss treatment progress and screen for any other medical and psychiatric comorbidities. The research team will send electronic postdiagnostic questionnaires to the caregiver and clinician to complete 1 to 3 (up to 10) days after this follow-up visit.

#### Interim Visit Forms

Clinicians will complete interim visit forms for any additional visits that may occur between study enrollment and the scheduled final 3-month follow-up visit.

#### Long-term Follow-up

Participants and their caregivers may be considered for enrollment if they choose to consent to an extension study to continue data collection related to long-term outcomes.

### Number of Sites Enrolling Participants

Up to 15 University of Missouri ECHO Autism clinicians in both rural and suburban areas across the United States will be recruited.

### Study Duration

Study enrollment is expected to take approximately 12 months. Patient participation will occur from the time the ECHO Autism clinician identifies a concern for ASD through +21 or −21 days of the 3-month follow-up visit.

### Potential Risks and Benefits of Participation

There are no physical risks associated with participation in the study. Caregivers may feel some psychological discomfort when answering questions about their children’s behaviors. Children might also feel some psychological discomfort when being filmed for the video analysis. Videos will be used to evaluate participants’ behaviors as part of the diagnostic process. The videos will be captured within the mobile app, stored on Amazon’s secure cloud service (Amazon S3), and analyzed by the device manufacturer through a secure web portal. By agreeing to participate in the study, participants will grant and release all rights, titles, and interests in the videos to the device manufacturer. Another potential risk is the possible release of sensitive medical, behavioral, or educational information. To mitigate the risk of releasing sensitive personal information, the device manufacturer will adhere to confidentiality protocols aligned with the US Health Insurance Portability and Accountability Act and FDA 21 Code of Federal Regulations Part 11, as well as other federal, national, and local laws and regulations, to protect the privacy of personal information. All content within the mobile app will be stored on Amazon S3 and analyzed by the device manufacturer through a secure web portal. When data are published, they will be anonymized in a manner that prevents the identification of specific caregivers or participants. To the best of the manufacturer’s knowledge, there were no data or security breaches in any prior studies involving the device.

A potential benefit of the study is that device use could support ECHO Autism clinicians in identifying participants with ASD earlier than they would otherwise have been identified, thus enabling earlier therapy, which is known to positively affect long-term outcomes.

### Participant Withdrawal or Termination

Participation is completely voluntary. Caregivers may withdraw consent for study participation at any time by informing the principal investigator or the study staff. The principal investigator may also withdraw a participant from the study if determined that further participation would not be in the participant’s best interest. Participants may be discontinued by the study staff if determined unable to fully meet the requirements of participation, including the completion of study visits and necessary assessments. The reasons for discontinuation will be recorded for all participants. If lost to follow-up, the research team will attempt to contact the caregiver by telephone, followed by registered mail, to establish the reason for withdrawal as completely as possible.

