### Study Objectives

#### Primary Objective

The primary objective is to assess the time from the initial concern by the ECHO Autism clinician to diagnosis when using the device as part of the diagnostic pathway.

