### Statistical Analyses

#### Statistical and Analytical Plans

Descriptive statistics will be used to summarize the data. Continuous variables will be summarized as n, mean, SD, median, minimum, and maximum values. Categorical variables will be summarized as participant counts and related percentages.

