#### General Approach

All available data will be included in data listings and tabulations. Data will be summarized by participant counts and related percentages. In general, categorical data will be presented using counts and percentages, whereas continuous variables will be presented using mean, SD, median, minimum, and maximum values. Counts of observed and missing data will also be reported.

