#### Sample Size

This is a prospective study with up to 100 patient participants determined eligible for an evaluation for ASD and up to 15 ECHO Autism clinicians who conduct assessments.

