The device was also trained on a large and diverse data set in terms of race and ethnicity, socioeconomic status, and gender. Although the pivotal trial was not powered for statistical inference on these covariates, our initial analysis indicated no evidence of inconsistent device performance across these variables [39]. This finding is encouraging and points to the potential of the device to address some of the well-documented disparities in current diagnostic approaches whereby girls and African American and Hispanic children are misdiagnosed more often, as well as diagnosed at a later age, on average, than other groups [47,48].

The device itself and the overall study design have several constraints and limitations. Device use requires access to a smartphone and wireless internet, which not all low-income American families have [49]. In addition, the device is only available in English. Thus, many culturally and linguistically diverse potential participants will be excluded from the study. Selection bias may also be a concern in this study. For example, parents with a higher number of concerns about their child’s development may be more motivated to enroll in the study and complete all device inputs than parents with milder concerns. Attrition is another concern in this study as participation involves multiple steps and engagement over a 3-month period. Given the multiple steps involved, it is possible that study completers may end up representing a more motivated cohort than study leavers. The clinicians who will be recruited into the trial may also represent a biased sample, as by enrolling in ECHO training, they have already demonstrated an interest in enhancing their knowledge of developmental disabilities. In addition, owing to the ECHO Autism curriculum training they receive, clinicians may have more experience and background in ASD diagnosis than other primary care clinicians. In other settings, clinicians with less interest in ASD may be less motivated or confident in using the device and may be less willing to diagnose in the primary care setting.

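### Staff may end participation for not completing visits or assessments; used before diagnosis, this can lose the primary time in the slowest families and bias its mean or median downward

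*Protocol article*

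**What the plan says.** The rule is in Participant Withdrawal or Termination: "Participants may be discontinued by the study staff if determined unable to fully meet the requirements of participation, including the completion of study visits", extended in the same sentence to necessary assessments. It is discretionary, carries no threshold or time limit, and is separate from consent withdrawal, best-interest withdrawal by the investigator and loss to follow-up. The section adds: "The reasons for discontinuation will be recorded for all participants".

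Other relevant text in the protocol article:

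- Primary Objective: "The primary objective is to assess the time from the initial concern by the ECHO Autism clinician to diagnosis when using the device".
- Visit 2: the clinician combines the device output with other findings, then delivers any ASD diagnosis.
- Study Flow, Overview: data are collected at the end of the 3-month follow-up. Interim visit forms cover other visits.
- Abstract, Methods: review of standard clinical records is one of the sources of outcome data.
- Statistical and Analytical Plans: "Continuous variables will be summarized as n, mean, SD, median, minimum, and maximum values".
- General Approach: "All available data will be included in data listings and tabulations", and "Counts of observed and missing data will also be reported".
- Textbox 2: the share of patients with a determinate device result is a secondary item. Which patients form the denominator is not stated.
- Strengths and Limitations: attrition is named as a concern, because "study completers may end up representing a more motivated cohort than study leavers".

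**The concern.** The study asks whether the device fits into a primary care pathway and how long that pathway takes to reach a diagnosis. The steps a family may fail to finish (app download, caregiver questionnaire, two videos, a visit for the provider questionnaire) all come before the device output, and the output comes before visit 2. A family that stalls there is informative about both questions. The rule allows staff to end its participation for stalling.

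The child normally remains in routine care with the same clinician and may be diagnosed later. If study data collection stops at discontinuation, that date is not captured, and a summary of observed times has nothing to include for the child. Families slow with device steps are plausibly slow to reach diagnosis, so the reported time could describe the faster families. The article recognizes attrition as a limitation, yet keeps a staff-initiated route to it that the study could avoid.

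**Working it through.** **No figure in the plan to reproduce.** Sample Size gives only a cap: "This is a prospective study with up to 100 patient participants determined eligible for an evaluation for ASD". There is no precision, power or dropout input. What follows is illustration.

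**Step 1: when can the rule touch the primary time?** The sequence is concern, prescription, three device inputs, output, visit 2 (diagnosis), 3-month visit.

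- Discontinued before visit 2: the diagnosis date is lost unless records are still followed.
- Discontinued after visit 2, for example for a missed 3-month visit: the diagnosis has already been delivered, so the effect on the primary time is 0.

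**Step 2: size of the effect on the primary time.** Assumptions, none from the documents: time to diagnosis is lognormal with median 60 days and log-SD 0.6, so the mean is 60 × exp(0.6²/2) ≈ 72 days. A fraction d is discontinued before diagnosis and contributes no time. Three patterns were simulated with 400,000 draws: discontinuation unrelated to time; moderately related (probability 2 × d × rank, where rank runs from 0 for the fastest to 1 for the slowest); and the slowest fraction d lost. Entries are observed median / mean in days.

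| d | Unrelated | Moderately related | Slowest lost |
|---|---|---|---|
| 0% | 59.9 / 71.7 | 59.9 / 71.7 | 59.9 / 71.7 |
| 10% | 59.9 / 71.7 | 57.5 / 69.1 | 55.6 / 59.9 |
| 20% | 59.9 / 71.7 | 54.6 / 65.8 | 51.6 / 53.4 |
| 30% | 60.0 / 71.7 | 51.4 / 61.6 | 47.6 / 48.2 |

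Closed-form check at d = 20%:

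- Slowest lost: the median of those remaining is the original 40th percentile, 60 × exp(0.6 × −0.253) = 51.5 days.
- Moderately related: the median rank r solves r − 0.2r² = 0.5 × 0.8, so r = 0.438 and the median is 60 × exp(0.6 × −0.155) = 54.7 days.

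Both agree with the simulation to about 0.1 day.

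**Step 3: determinate-result percentage.** A family that never completes the inputs has no device result whether or not staff discontinue it. The count of determinate results is therefore unchanged by the rule, and only the denominator matters:

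rate per child prescribed = rate among completed submissions × (1 − non-completion)

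| Assumed rate among completers | 10% non-completion | 20% | 30% |
|---|---|---|---|
| 32% | 28.8% | 25.6% | 22.4% |
| 50% | 45.0% | 40.0% | 35.0% |
| 70% | 63.0% | 56.0% | 49.0% |

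At 32% the gap between the two denominators is 3.2, 6.4 and 9.6 points. The 32% is prompted by the statement in Device Development that the device facilitated evaluation in nearly a third of the pivotal cohort. Applying it to completed submissions is an assumption, as are the non-completion rates.

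**The case against.** The strongest reply is that ending participation is not exclusion from analysis. A reader might infer from the rule that failures are removed, so that feasibility is overstated and both the primary time and the determinate percentage are biased. The documents do not support that. Nothing says discontinued participants leave the tables. Reasons are recorded for everyone, all available data are used, and missing counts are reported, so failures stay countable. Nor does the text say that record review stops at discontinuation; that is an inference from silence, and post-discontinuation handling may be set out in the full protocol or analysis plan, which are not shown. This reply stands, and it limits the point to a conditional risk.

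Three further replies have weight:

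- Textbox 2 measures efficiency and feasibility of the diagnostic process through self-efficacy, certainty, perceived-barrier and practice-pattern questionnaires. Input completion is not the named feasibility outcome. This stands, though caregiver barriers to app use are listed and non-completion bears directly on them.
- The determinate percentage turns on its denominator, and a rate per completed submission is a legitimate measure of how often the device abstains. This stands in full.
- The primary objective concerns time when the device is used, so a child who never completes it might fall outside the question. This stands in part: such a conditional time can be reported, but it needs the number of children left out beside it.

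What the reply does not answer is that using all available data covers only what was collected. Recorded reasons and missing counts show how many were lost without supplying their diagnosis dates, and an analysis plan cannot restore dates that were never captured.

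**Conclusion.** The point holds as a conditional risk to the primary end point. Staff discontinuation for non-completion before visit 2 can end observation of time to diagnosis in the families likely to be slowest. A mean or median of observed times is then too short if discontinuation is related to slowness. There is no bias if it is unrelated or occurs after diagnosis.

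Under the stated assumptions and 20% discontinuation, the median falls from 60 days to between 52 and 55, and the mean from 72 to between 53 and 66. These show scale only; the documents give neither a dropout rate nor a distribution of times.

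The stronger conclusion, that the rule removes failures from the analysis or by itself biases the determinate-result percentage, is not supported. For that percentage the remaining matter is a denominator to be stated, worth about 3 to 10 points at an assumed 32% and 10% to 30% non-completion. Because the loss can be prevented from records the study already plans to review, the change is worth making.

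**What to change.** Amend the sentence in Participant Withdrawal or Termination so that failure to complete device steps or visits is recorded as an outcome and does not by itself end data collection. Unless consent is withdrawn, diagnosis date, referral and treatment start continue to be taken from the routine clinical records already under review.

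In reporting:

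- Give the number of children without a diagnosis beside the primary mean and median.
- Give the determinate-result percentage among all children prescribed the device, with the rate among completed submissions second.

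The cost is one amended sentence, slightly more record review for a cohort capped at 100, and one added table. The downside is a possibly lower headline determinate rate. The Results section reports 41 participants enrolled by June 2022, so the sooner the wording changes, the fewer diagnosis dates need to be recovered afterwards.

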### Study Objectives

#### Primary Objective

The primary objective is to assess the time from the initial concern by the ECHO Autism clinician to diagnosis when using the device as part of the diagnostic pathway.

#### Secondary Objectives

Secondary objectives include the collection and analysis of data from both the ECHO Autism clinician and caregiver participants to learn about the information described in Textbox 2.

Data collected for secondary objectives.
**Data collected for secondary objectives**
Patient outcomes correlating with time to initiating therapy following a positive autism spectrum disorder (ASD) diagnosisDistance from patient home to nearest ASD specialist centerLevel of clinician self-efficacy in using the device as part of the evaluation and diagnosis of children with suspected ASDQualitative data on the following: caregiver satisfaction with the diagnostic process; time from caregiver concern to diagnosis; clinician certainty rating for diagnostic determination; clinician satisfaction with using the device as part of the Extension for Community Health Outcomes (ECHO) Autism diagnostic process; caregiver perception of the device with validated questionnaire; determination of whether the use of the device enhances the efficiency and feasibility of the ECHO Autism Communities diagnostic process; likelihood to recommend (clinician and caregiver); efficiency and feasibility of ECHO Autism Community–based diagnostic process, as measured by self-efficacy, certainty ratings, perceived barriers, and practice patterns questionnaires; percentage of positive outcomes correlating with shorter durations between diagnosis and treatment; percentage of caregivers who feel they received a high-quality evaluation; percentage of clinicians with increased self-efficacy in using the device as part of the diagnostic process; percentage of clinicians finding the device helpful in the diagnostic process; percentage of positive device perceptions from caregiver; barriers to app use for caregivers; clinician-perceived barriers to practice implementation of deviceAssessment of insurance coverage or reimbursement (although insurance will not be billed for this study)Amount of time required for clinicians to make a diagnosisPercentage of clinician participants reporting a positive change in practice flow because of using the device as part of their diagnostic processPercentage of patients for whom the device can provide a determinate result (ASD positive or negative)Summary of interventional treatments recommended by the clinician following diagnosisChanges in clinician clinical practice flowChange in quality of life measuresTime associated with device use

### Data Collection Instruments and Schedule of Assessments

#### Clinical History

Details of participants’ clinical and medical histories will be reviewed and captured, including the description and timing of the initial concern for ASD.

#### Diagnostic Procedures

Diagnostic procedures will be completed according to the ECHO Autism Communities standard of care, as determined by the treating clinician in routine clinical practice. Details of any such procedure will be captured throughout the study, including the follow-up period after a participant has received diagnostic results.

#### Therapeutic Interventions

Any new therapeutic interventions recommended by the ECHO Autism clinician will be captured at time points 1, 2, and 3 and for any interim visit. Once a recommendation has been made, data will be collected during subsequent visits to indicate patient compliance with the recommendations.

All data collection instruments are listed and described in Textbox 3.

Data collection instruments.
**Caregiver questionnaire (device input 1)**
This is not a stand-alone assessment. The caregiver questionnaire will be completed within the mobile caregiver app upon receipt of the access code following completion of the informed consent form. This is an 18- or 21-item questionnaire that collects details related to the caregiver’s observations of the participant’s developmental behaviors.
**Video analyst questionnaire (device input 2)**
This is not a stand-alone assessment. Video analysts will answer a 28- or 33-item age-dependent questionnaire in the video analyst portal after viewing the 2 short video submissions uploaded by the caregiver. Video analysts will evaluate the observed behaviors by answering a series of multiple-choice questions evaluating phenotypic features of autism spectrum disorder (ASD) such as nonverbal and verbal communication, social interaction, unusual sensory interests or reactions, stereotypic or repetitive motor movements, use of objects, or speech on the combinative videos.
**Health care provider questionnaire (device input 3)**
This is not a stand-alone assessment. The clinician or telehealth provider will schedule a visit with the caregiver and participant (which can be remote). During this visit, the participant must be available for observation. The clinician or telehealth vendor will complete the 13- or 15-item questionnaire within the health care provider portal. The questionnaire addresses aspects of the child’s behavior and development.
**Device output**
Device output is produced by the device summarizing findings after algorithmic analysis of the 3 device inputs and contains one of 3 possible results: positive ASD, negative ASD, or no result. It is to be used by the clinician as part of the Extension for Community Health Outcomes (ECHO) Autism Community–based diagnostic process.
**Measure of processes of care**
This measure assesses the family’s perceptions of the care they and their child receive within a particular setting. It is a means to assess the family-centered behaviors of clinicians. This is a validated measure that has been adapted for this study.
**ECHO Autism caregiver presurvey**
This survey collects initial demographic information regarding each family and assesses the family’s initial perception of the ECHO Autism clinician as they begin the diagnostic process.
**ECHO Autism caregiver postdiagnostic survey**
This survey assesses the caregiver’s satisfaction with the services they received.
**ECHO Autism clinician preproject survey**
This survey measures the ECHO Autism clinician’s self-efficacy, perceived barriers, and satisfaction with the current ECHO Autism standard-of-care procedure.
**ECHO Autism clinician postproject survey**
This survey measures the self-efficacy, perceived barriers, and satisfaction with the use of the device as part of the ECHO Autism standard-of-care procedure.
**ECHO Autism 3-month follow-up questionnaires**
The purpose of these questionnaires is to address the data points required for the study’s secondary and exploratory objectives.
**ECHO Autism interim visit form**
The purpose of the form is to summarize any visit from a research participant occurring between the time of concern and the 3-month follow-up visit.

### Statistical Analyses

#### Statistical and Analytical Plans

Descriptive statistics will be used to summarize the data. Continuous variables will be summarized as n, mean, SD, median, minimum, and maximum values. Categorical variables will be summarized as participant counts and related percentages.

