**Objective:**

This study aims to assess the feasibility and impact of integrating an AI-based ASD diagnosis aid into the ECHO Autism STAT diagnosis model. The time from initial ECHO Autism clinician concern to ASD diagnosis is the primary end point. Secondary end points include the time from initial caregiver concern to ASD diagnosis, time from diagnosis to treatment initiation, and clinician and caregiver experience of device use as part of the ASD diagnostic journey.

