### The ECHO Autism Primary Care Model

ECHO Autism primary care [41,42] is a virtual learning program in which primary care clinicians receive guidance from ASD experts regarding best practices for ASD screening, identification, and management of medical and psychiatric comorbidities. The diagnostic component of the ECHO Autism primary care model involves training clinicians to conduct diagnostic assessments for ASD using the Screening Tool for Autism in Toddlers and Young Children (STAT), a level 2 ASD screener used as a diagnostic observational measure. The ECHO Autism STAT model provides training and mentorship to equip clinicians to diagnose ASD in cases that are clear and unambiguous and appropriately identify and refer complex cases for further assessment [43]. A 12-month pilot study with 18 participating clinicians was conducted using the ECHO Autism STAT model [43]. In this study, participating clinicians presented the results of their assessment to the ECHO Autism expert hub team for specialist input before guiding the diagnostic pathway to include either a diagnosis of ASD or a referral for further specialist evaluation. This pilot study showed that 73% of the participants reported acceptance of referrals for ASD diagnostic evaluations following program completion, and 80% reported an increase in the number of children with ASD in their caseloads. In addition, the pilot demonstrated a 2- to 6-month decrease in time to access services when compared with standard-of-care diagnostic pathways [41]*.*

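### The only stated summary for the primary time-to-diagnosis end point uses observed values alone, so it describes diagnosed children and understates the delay to the extent that others are referred, pending, withdrawn or cut off

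*Protocol article*

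**What the plan says.** The Abstract (Objective) states: "The time from initial ECHO Autism clinician concern to ASD diagnosis is the primary end point". The Primary Objective section is looser: "The primary objective is to assess the time from the initial concern by the ECHO Autism clinician to diagnosis when using the device". It does not say whether a finding that the child does not have ASD also ends the clock.

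The analysis is descriptive throughout. Statistical and Analytical Plans says "Descriptive statistics will be used to summarize the data" and then "Continuous variables will be summarized as n, mean, SD, median, minimum, and maximum values". General Approach repeats the same statistics and adds: "Counts of observed and missing data will also be reported". Neither section names the primary end point or reserves a different method for it.

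The population is wider than children with ASD. Sample Size says: "This is a prospective study with up to 100 patient participants determined eligible for an evaluation for ASD". Visit 2 provides for delivery of a diagnosis to children judged to meet ASD criteria. Visit 3 is timed from that diagnosis, and Study Duration ends participation at visit 3. The ECHO Autism Primary Care Model section says the model trains clinicians to diagnose clear cases and to "appropriately identify and refer complex cases for further assessment".

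**The concern.** The end point is a time to an event, but the stated statistics need an observed time for each child who contributes. A child whose diagnosis has not yet come, or who leaves first, is known to have waited at least as long as observed. The stated summary drops that information and records the child as missing.

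The mean and median then answer how quickly the diagnosed children were diagnosed. The objective asks how long a child waits once the clinician has a concern. The two answers part company when undiagnosed children are the slower ones. This matters because the Conclusions tie the study to shorter diagnostic delay, and an understated delay would flatter the device pathway.

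**Working it through.** The article gives no expected time to diagnosis, dropout rate, referral share or ASD share, so there is no figure of its own to reproduce. All times and shares in steps 2 to 4 are assumptions.

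**1. Which children have a value under the stated summary**

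- Diagnosed with ASD on study: time observed.
- ASD ruled out: no time to ASD diagnosis. If any determination counts as the event, there is a time.
- Referred without determination (ECHO Autism Primary Care Model; Conclusions): no time on study.
- Still pending: no time, and no stated end of observation, because visit 3 is anchored on an ASD diagnosis.
- Withdrawn or lost (Participant Withdrawal or Termination; Strengths and Limitations names attrition as a concern): no time.
- Cut off at study end: no time. This can happen because the Abstract (Methods) caps the study at 12 months, while Study Duration gives about 12 months to enrollment alone, with a 3-month visit still to follow. Results expects data collection through 2022 after an April start, which is about 9 months.

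**2. Cutoff with staggered entry**

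Assume exponential times with true median 60 days, so λ = ln 2 / 60 = 0.01155 per day, and observation windows uniform on 0 to a days.

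- Share observed = 1 − (1 − e^(−λa)) / (λa).
- a = 270: λa = 3.12, share = 1 − 0.956/3.12 = 69%. Median of observed times: 40 days.
- a = 365: λa = 4.22, share = 1 − 0.985/4.22 = 77%. Median of observed times: 45 days.
- Every child followed for 365 days: 99% observed, median of observed times 59 days.

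In simulations of 200,000 children, Kaplan-Meier returned 60 days in all three cases. With true medians of 30 and 120 days, over these windows and fixed cutoffs of 90 and 180 days, the observed-only median ran from 25 to 30 days and from 39 to 100 days respectively. With a true median of 120 days and a 90-day cutoff, only 41% were observed and the Kaplan-Meier median was not reached.

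**3. Other routes, also with exponential times**

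- Withdrawal at constant hazard, with probability d of leaving before diagnosis: observed/true = 1 − d, giving 0.90, 0.80 and 0.70 for d = 10%, 20% and 30%.
- Slowest share u never diagnosed on study: the observed median is the (1 − u)/2 quantile of the true distribution, so the ratio is −ln((1 + u)/2) / ln 2. For u = 10%, 20% and 30% this is 0.86, 0.74 and 0.62.
- Only correctly ruled-out children lack a time: ratio 1.00, so no bias for children with ASD.

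**4. Why referral should not be treated as ordinary censoring**

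Assume a share p is diagnosed in the pathway with lognormal times F (median 45 days, log-SD 0.5). The rest are referred, at times that also follow F, and are diagnosed later with median 240 days and the same log-SD. The observed-only median is 45 days whatever p is.

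| p | All-children median | Kaplan-Meier, referral censored: (1 − F)^p = 0.5 | Cumulative incidence, referral competing: pF = 0.5 |
|---|---|---|---|
| 75% | 56 | F = 0.603, 51 days | F = 0.667, 56 days |
| 60% | 72 | F = 0.685, 57 days | F = 0.833, 73 days |
| 50% | 104 | F = 0.750, 63 days | F = 1, not reached at any finite time |

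Censoring at referral assumes that referred children would have been diagnosed at the same rate as those who stayed. In this illustration that removes only part of the bias: at p = 50%, (63 − 45)/(104 − 45) = 31% of it. Cumulative incidence makes no such assumption about referred children.

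**The case against.** The quoted sentence is a general rule for continuous variables. The article condenses a fuller protocol, and an analysis plan not shown may add a time-to-event method. The study is noninterventional, single-group and descriptive, with no test, comparator or threshold. Missing counts will be reported, reasons for discontinuation recorded, and attrition is acknowledged as a limitation.

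Much of this stands. That the rule governs the primary end point is an inference, though a strong one, since no other method is stated and none is reserved. The missing count shows how many children have no value, but it does not correct the mean or median or separate ruled-out children from those still waiting.

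Three stronger readings are tempting, and the article does not support them:

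- **The bias always favors the device.** Ruled-out children cause none, and with near-complete observation it is about nil. Under the Primary Objective's wording, a rule-out may even count as an event.
- **The undiagnosed group must be large, because the device aided evaluation in only nearly a third of its pivotal cohort.** That figure concerns the device. In this study the clinician decides (Visit 2), and a device abstention does not prevent a diagnosis.
- **The absence of a confidence interval and of an allowance for clustering by clinician is an error.** These are matters an article may leave to the analysis plan.

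**Conclusion.** The point holds in a conditional form. The article pairs a time-to-event primary end point with a summary that needs an observed value. It gives no rule and no end of observation for children without an ASD diagnosis. Followed as written, the result describes diagnosed children only and is too short to the extent that others are referred, pending, withdrawn or cut off.

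The direction for those children is clear; the size is not known. Under the exponential assumption with staggered entry, a true median of 60 days is reported as about 40 to 45. With a year of follow-up for every child it is reported as 59. No hypothesis test depends on the choice, but the headline figure does, so it should be settled before the analysis planned for 2023.

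**What to change.** 1. State whether the event is an ASD diagnosis or any diagnostic determination, and align the Abstract with the Primary Objective.
2. Set an end of observation for every enrolled child with a clinician concern, including those never diagnosed. Reconcile the 12-month study duration with about 12 months of enrollment plus the 3-month visit.
3. Report the cumulative incidence of ASD diagnosis over time, with 'ASD ruled out' and 'referred without determination' as competing outcomes. Censor only for withdrawal, loss to follow-up or study cutoff.
4. Give the percentage diagnosed or determined by fixed times (for example 30, 60 and 90 days), the median where it is reached, and the number of children in each category.
5. Keep the diagnosed-only mean and median as a supplementary summary, labelled as such.

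The cost is revised wording, a last-contact date for each child and slightly more programming. The headline delay may be longer, or its median may not be reached.
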